### Allocation concealment

The randomization lists will be kept in opaque envelopes by the non-investigator on the team which are ordered, identical, and sealed with adhesive.

### Implementation

The participants will be consecutively enrolled and distributed into experimental and control groups by researchers according to the randomized sequences generated who will not participate in assessing outcomes. Another group of researchers responsible for analyzing results will be blind to the grouping of subjects and will not participate in the treatment. The executors of this trial and subjects will not be blinded to the treatment assignment.

## Interventions

### Explanation for the choice of comparators

The choice of the comparator is based on the current treatment of myopia in clinical.

### Intervention description

The vision acuity training of this study is conducted in the schools, and school leaders are fully aware of this project, support, and cooperate with the research work. Relevant teachers will be designated by the schools to be responsible for this project with respect to the specific matters concerned. The study will be conducted in two phases over a period of 8 months, with a training period of 30 days in each phase and a follow-up of 3 months. No interventions will be conducted during the treatment period and follow-up period. One visual acuity examination will be performed in each of the two phases at months 1, 2, and 3 of the follow-up.

### Phase 1

#### Experimental group

Two sets of vision acuity training movement verbal commands will be applied in the experimental group. In order to facilitate the subjects to follow the verbal commands in a uniform, standardized way, the related audio and standard movements will be recorded.

The first set of audio and video content are relatively rich, lasting about 1 h, and the audio and video will be projected in the classroom on the first and eighth days of training, with the subjects following the verbal commands and the movement demonstrations in the video. Visual training tutors (trained in procedures and methods) will be responsible for audio and video presentations.

The second set of audio and video content are relatively concise, approximately 15–20 min in length, and the subjects will be trained under the schools’ uniform deployment for the remaining 28 days.

Due to the uninterrupted daily vision acuity training for 30 days, it is recommended to use the last self-study class at the schools to ensure that the students’ normal studies are not interrupted; students will still be required to come to get trained at their school or a designated location confirmed with the schools on Saturday.

#### First training

The first set of audio and video training exercises will be projected in the classroom by the vision acuity training tutor, and the students will be guided by the audio-visual movements and verbal commands to perform the following exercises.
Abdominal breathing: Inhale through the nose, exhale through the mouth, bulge abdomen while inhaling, tighten abdomen while exhaling; start doing abdominal breathing when hearing the words of “adjust your breath and inhale.”Eye-warning exercise: Rub your hands more than 30 times, cover your eyes with the palms, place thumbs on the temples, clasp four fingers on your forehead, and leverage the temperature of your palms to warm eyes; after the temperature gradually dissipates, use Yuji acupoints of the palms to gently press your eyes 5 times, with moderate intensity; start eye-warning exercise when you hear the words “get ready to press” and “quickly rub your hands” during training.Healthy vision exercise: Press both hand palms on your ears, place fingers on the back of your head; do not move the palms, and use fingers to gently tap the back of your head. During the training, when you hear “healthy vision exercise,” start doing it.Activate Shixuan acupuncture point: Tap your fingers on your palm, shake your palm, and make an arrow shape.Play the “1-Audio,” turn off the lights in the classroom, close the curtains, and try to create a dark environment. Remain quiet the entire time. Close your eyes until the audio says to open them. Follow the audio to imagine and do movements, e.g., “Use the fingertips of one hand to gently touch the center of the palm of the other, and then shake your hand vigorously.”Play the “C-video,” a video about lotus flowers to stimulate the imagination and match the 2-Audio with the images that appear in the video. For example, “On a calm lake, you can definitely see the vivid color of the lotus flowers and the greenish-blue leaves of the lotus .......”Demonstration and correction. Make a hollow bowl shape with your hands (thumbs on the second knuckle of your index finger) and clasp them over your eyes, with palms facing your eyes.Play “2-Audio” and do the eye stretches: Close your eyes and move them from front to back as if a train is moving back and forth in a tunnel.Play “3-Audio” and listen to the audio with your hands in a hollow bowl shape over your eyes the whole time. When the audio says “in,” put pressure on your eyes for 1 s, and when it says “out,” relax your eyes and perform the related imagery and actions. When the audio says “pull” in future exercises, let your eyes enter a state just like going into a tunnel, hold for 1 s, and then relax.Play “D-Video (Ball of Light)” to stimulate imagination and introduce natural light.Play “4-Audio” to build up the confidence of myopia sufferers to restore their eyesight.The above training will be repeated on the 8th day to intensify the effect, for 1 h.

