#### Control group

The control group will be given Chinese eye exercises in the first stage of the trial. On the first day and the eighth day of the trial, the school teachers who have received training in Chinese eye exercises will give instructions on finding the positions of acupoints, massage intensity, direction, and frequency according to the standard Chinese eye exercises Assessment Form to ensure that the students can perform the eye exercises independently and with high quality. For the remaining 28 days, subjects will be in a uniform classroom for 15–20 min of daily Chinese eye exercises, acupoints: Jingming, Zanzhu, Yuyao, Tongziliao, Sizhukong, Taiyang, Chengqi, and Sibai.

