### Primary observation indexes

Visual acuity training aims to improve naked eye visual acuity, which affects life and work and will be used as the main observation index. Visual acuity tests were performed before and after each training session for the first 7 days, once a week after 7 days of training and at the first, second, and third months of follow-up, respectively.

The specification for visual acuity testing is based on the “Expert Consensus on Workflow of Myopia Screening in Children and Adolescents (2019)” [21]. The international standard logarithmic visual acuity chart is adopted. During the measurement, the subjects stand 5 m away from the visual acuity chart and cover the contralateral eyes without squinting and oppression. The covered eyes are examined first in the right eye and then in the left eye. If the inspector can identify half or more of the visual markers, check them line by line from top to bottom and ask the subjects to say or gesture the direction of the gap of the visual markers within 5 s. The last line of the visual markers that is correct will be the testee’s vision of that eye. For example, if row 4.8 cannot be identified, check upward until half or more of the rows can be identified.

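### Acuity is the unblinded child's own answer with no forced-choice rule, and only the experimental arm hears a confidence message, so a difference in willingness to guess can enter the primary comparison

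*Protocol article*

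**What the plan says.** **Experimental arm.** Under First training, the first audio-video set includes a fourth audio track played "to build up the confidence of myopia sufferers to restore their eyesight". The whole session is given again a week later: "The above training will be repeated on the 8th day to intensify the effect".

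**Control arm.** "The control group will be given Chinese eye exercises in the first stage of the trial". On days 1 and 8 trained school teachers "give instructions on finding the positions of acupoints, massage intensity, direction, and frequency". No confidence message is described, and Table 1 gives the first audio-video set in phase 1 to the meditation group only.

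**Outcome.** The section Primary observation indexes names the endpoint: "Visual acuity training aims to improve naked eye visual acuity, which affects life and work and will be used as the main observation index". The examiner is to "ask the subjects to say or gesture the direction of the gap of the visual markers within 5 s". A child who fails a row is handled by the instruction to "check upward until half or more of the rows can be identified". The same paragraph also says that the last correct line is the recorded vision. It does not say whether a child may decline a symbol. Tests are done before and after each session in the first 7 days, then weekly, then at months 1, 2 and 3.

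**Blinding.** Under Implementation: "The executors of this trial and subjects will not be blinded to the treatment assignment". Those described as blinded or masked are the researchers analysing results, data entry staff and statisticians (Implementation; Quality control).

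**The concern.** A chart reading depends on what the child can see and on whether the child is willing to answer when unsure. If both arms have the same willingness, it adds noise. If one arm is encouraged to expect recovery and the other is not, it can add a difference in means.

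The plan has the conditions for this: unblinded children, an expectancy message in one arm, and a test that leaves the child free to stop. One acuity test directly follows the day 1 session. Masking the examiner would not help, because the shift lies in the child's response, and a masked examiner would record it faithfully. Masked analysts cannot remove it either.

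Study design says the trial will evaluate efficacy objectively, and Second phase makes phase 2 depend on the phase 1 comparison. A shift in response behaviour would be read there as a gain in vision.

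**Working it through.** **Inputs from the protocol (Sample size).** Means 4.98 and 4.92, SDs 0.14 and 0.24, 760 + 380 children, 20% dropout, two-sided 0.05.

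- Planned difference: 4.98 − 4.92 = 0.06.
- Completers: 760 × 0.8 = 608 and 380 × 0.8 = 304.

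The stated base size of 380 + 190 was not reproduced. The unequal-variance formula gives 394 + 197 before dropout and 494 + 247 after. That is a separate matter and does not affect this point, which uses the final 760 + 380.

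**Assumptions, not in the documents.** Four possible gap directions, 4 or 5 symbols per row, rows 0.1 apart, a row passed at half or more of its symbols, and one further row attempted.

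**Step 1: difference needed for significance.** SE = √(0.14²/608 + 0.24²/304) = 0.0149. Critical difference = 1.96 × 0.0149 = 0.029. Children are treated as independent.

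**Step 2: gain per child who attempts one further row over one who declines.** Gain = 0.1 × P(row passed), from the binomial distribution.

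| Chance correct per symbol | Symbols (needed) | P(pass) | Gain | Share of 0.06 |
|---|---|---|---|---|
| 0.25 (pure guess) | 4 (2) | 0.262 | 0.026 | 44% |
| 0.25 (pure guess) | 5 (3) | 0.104 | 0.010 | 17% |
| 0.40 (partial information) | 4 (2) | 0.525 | 0.052 | 87% |
| 0.40 (partial information) | 5 (3) | 0.317 | 0.032 | 53% |

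**Step 3: from child to arm.** Bias = gain × (attempt rate in the experimental arm − attempt rate in controls). With no true effect, P(significant) = P(|Z + bias/SE| > 1.96), against a nominal 0.05.

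| Difference in attempt rates | Bias, pure guess | P(significant) | Bias, 40% correct | P(significant) |
|---|---|---|---|---|
| 25 points | 0.003 to 0.007 | 0.05 to 0.07 | 0.008 to 0.013 | 0.08 to 0.14 |
| 50 points | 0.005 to 0.013 | 0.06 to 0.14 | 0.016 to 0.026 | 0.19 to 0.42 |
| 100 points | 0.010 to 0.026 | 0.11 to 0.42 | 0.032 to 0.052 | 0.57 to 0.94 |

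A pure guess at one row stays below 0.029 even with a complete split between arms. At 40% correct, the bias reaches 0.029 only if attempt rates differ by 0.56 (0.0292/0.0525) to 0.92 (0.0292/0.0317).

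**Step 4: sensitivity to the assumptions.**

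- If the child keeps guessing after each passed row, the pure-guess gain is 0.1 × p/(1 − p) = 0.012 to 0.035. The top value would give 0.029 only with attempt rates differing by about 0.82 (0.0292/0.0354).
- If the sentence about the last correct line means every symbol correct, a pure guess passes with probability 0.25⁴ = 0.004 or 0.25⁵ = 0.001, and the gain all but vanishes.

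The choice of pass rule therefore decides much of the size, and the printed text does not settle it.

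**The case against.** **The message is part of the treatment.** Background presents the method from a psychosomatic standpoint that aims to stimulate self-healing, and Discussion describes a mix of movement, breathing and imagination. Testing that package whole is a legitimate question. This stands. Removing the track, or playing it to controls, would change the question. It would not equalise expectation either, since children still know their arm and the other imagery is suggestive too.

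**The trial declares itself open-label.** True, but that discloses the problem without limiting it.

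**The gap is partly silence.** The procedure cites an expert consensus that is not at hand and may contain a response rule. This stands as a caution. Still, the article prints distance, eye order, time limit and pass rule, and two of its sentences on passing do not agree.

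**The message is brief and an objective measure exists.** The track is played on two days, while acuity is followed to month 3, and persistence of its effect is not shown. Refraction after pupil dilation is collected in both arms and is unaffected by guessing at the chart. Both limit the concern, but refraction is only a secondary index and does not repair the primary one.

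**A stronger reading.** A reader might infer that suggestion and guessing alone would produce a significant result. The documents do not support that. They do not show that the message changes attempts at all, and a significant average shift needs partial information or run-on guessing together with a large difference in attempt rates.

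**Conclusion.** The point holds as a limited one. An arm-dependent willingness to attempt a row can enter the primary comparison and cannot be separated from a visual change, whoever examines the child. Its size is unknown. Under the stated assumptions it is 0.010 to 0.026 per additional child who attempts on a pure guess, or 0.032 to 0.052 at 40% correct per symbol, multiplied by the difference in attempt rates.

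With a 25-point difference in attempt rates, the false-positive rate would be about 0.05 to 0.07 for pure guessing and 0.08 to 0.14 with partial information. This is a possible inflation of the estimate and the error rate. It does not show that a positive result would be spurious, and it gives no reason to alter the recordings. It merits repair mainly because the repair is cheap.

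**What to change.** Under Primary observation indexes:

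1. Make the test forced-choice in both arms at every visit. The child answers every symbol of each row presented until a row is failed, and saying that a symbol cannot be seen is not accepted as an answer.
2. State one pass rule, reconciling the half-or-more criterion with the sentence on the last correct line, and correct the wording that applies the criterion to rows where symbols seem to be meant.

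Leave the recordings as they are. In the conclusion, attribute any effect to the whole package, including its confidence message.

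The cost is a few sentences of protocol text, slightly longer testing and some added guessing noise, equal in both arms. No extra staff or visits are needed.

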
#### Daily vision acuity training

Guided by the second set of audio and video movement verbal commands, the subjects perform self-rehabilitation exercises.
Ocular exercises: keep body and head still, torso upright, move only eyes, four 8-tempos per part.

In the first part, both eyes look up and down to the left. In the second part, both eyes look up and down to the right. In the third part, both eyes look to the left to the right. In the fourth part, both eyes turn clockwise. In the fifth part, turn both eyes counterclockwise. In the sixth part, close your eyes hard and then open them to look up. In the seventh part, close your eyes for a moment to control the time.
(2)Eye-warming exercises: same movements as before, 12 movements per day(3)Vision acuity exercise: same movements as before, 24 movements per day(4)Character card stretching: 10 min of training, with results recorded on an observation chart. Character cards (Chinese characters of different sizes) are placed on a well-lit wall at the subject’;s eye level. Find the farthest place where you can see the card clearly, that is, about 10–15 cm back where you cannot see the card clearly. Let your eyes stretch 6 times for 1.5 s each (eye movement, stretching backwards), without blinking, stare at the characters for 10 s, step back 15 cm, and repeat the above movements until you are unable to see the location of the character card after stretching. If the training time is less than 10 min, switch to a second character and repeat the above steps; if it has reached 10 min, end the exercise and take notes.

#### Control group

The control group will be given Chinese eye exercises in the first stage of the trial. On the first day and the eighth day of the trial, the school teachers who have received training in Chinese eye exercises will give instructions on finding the positions of acupoints, massage intensity, direction, and frequency according to the standard Chinese eye exercises Assessment Form to ensure that the students can perform the eye exercises independently and with high quality. For the remaining 28 days, subjects will be in a uniform classroom for 15–20 min of daily Chinese eye exercises, acupoints: Jingming, Zanzhu, Yuyao, Tongziliao, Sizhukong, Taiyang, Chengqi, and Sibai.

#### Second phase

After the completion of the first phase of the randomized controlled study, data will be collected and compared between the vision acuity training group and the Chinese eye exercise group.

The second phase will be carried out based on the experimental results of the first phase. If the first phase showed that the visual training effect was not significantly better than eye exercises, the trial was terminated. If the data proved that the effect of the meditation group was not superior to the control group, and the results were statistically significant, the second phase of the experiment will be carried out.

Since the purpose of this study is to improve the naked eye visual acuity that affects life and work, the experimental group has achieved this effect in the first stage. In order to ensure the maximum benefit of the subjects, only the control group and the experimental group of the first stage were given the same treatment plan in the second stage, namely guided meditation for vision acuity training. The results of phase 2 subjects (the control group at phase 1) were compared with the results of eye exercises at phase 1.

The subjects in this study are adolescent students with simple myopia and no other comorbidities of chronic diseases. If the subjects need to combine medication due to cold or other reasons, they should be recorded promptly.

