### Statistical analysis

Multiple factors that affect this trial will be taken into consideration. Participates from different areas with similar school level will be stratified. A stratified randomizing method will also be adopted according to region, age, gender, etc. Similar stratified groups will be compared; the experimental and the control groups are launched within the same school.

We will use a linear mixed model to analyze incorporating repeated measures. Firstly, visual acuity is independent among subjects and is the primary indicator of observation. Otherwise, it will be measured at the end of each training session and followed up for 3 months. That is important to model the correlation of these repeated measurements.

Statistical analysis using SPSS 20.0 will be performed, and data management software will be used to construct the database. Dedicated staff will be assigned to oversee the management of electronic data, and a clinical research team will be deployed for data entry, validation, reporting, and answering questions. Normally distributed variables will be expressed as their mean and standard deviation (SD), and frequency (percentage) for categorical variables. Baseline characteristics between the intervention and control groups will be compared by performing a two-sample *t*-test and Wilcoxon rank-sum test for continuous variables with and without normal distribution, respectively. All *P*-values are 2-sided and considered statistically significant when less than 0.05.

Primary and secondary observation indexes will be analyzed by the superiority test depending on the treatment, using Per Protocol Set (PPS) and Full Analysis Set (FAS) datasets. The indices of safety evaluation will be analyzed using the Save Set (SS) dataset.

According to the ophthalmic disease efficacy evaluation standard in the Guidelines for Clinical Research of Traditional Chinese Medicine New Drugs:
Cure: visual acuity to normal (5.0)Significant effect: visual acuity improved by 4 lines or more with a visual chartImprovement: visual acuity improved by 2 lines or moreIneffective: visual acuity improved by less than 2 rows or decrease

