## Trial status

At the time of submission, the formative research has been completed and recruitment is ongoing. The first participant will be enrolled in December 2021. Patient recruitment is estimated to be completed around September 2023. The current protocol is version 3.0 of 30-10-2021.

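### The rule for moving from phase 1 to phase 2 contradicts itself: a significantly worse result triggers both actions, and a significantly better result triggers neither.

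*Protocol article*

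**What the plan says.** The Second phase section opens with a gate: "The second phase will be carried out based on the experimental results of the first phase". Two sentences then define it.

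- Stopping: "If the first phase showed that the visual training effect was not significantly better than eye exercises, the trial was terminated".
- Continuing: "If the data proved that the effect of the meditation group was not superior to the control group, and the results were statistically significant", in which case "the second phase of the experiment will be carried out".

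The next paragraph explains why the phase 1 control group then receives the meditation training. Its premise is that "the experimental group has achieved this effect in the first stage", and its stated aim is to give subjects the most benefit.

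The Statistical analysis section sets the yardstick: "All *P*-values are 2-sided and considered statistically significant when less than 0.05". It describes the tests of the primary and secondary indexes as superiority tests.

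On timing, the Second phase section places the group comparison after phase 1 has been completed. The Intervention description says: "The study will be conducted in two phases over a period of 8 months". Table 1 lists phase 2 directly after the month 3 follow-up column. Trial status puts first enrolment in December 2021 and adds: "Patient recruitment is estimated to be completed around September 2023".

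**The concern.** The two conditions should divide the possible phase 1 results between them, with one action for each result. They do not. The continuing condition describes a result that the stopping condition already covers, and neither condition covers the result that the trial is designed to find. Anyone applying the rule would have to override its words or rely on the next paragraph to guess what was meant.

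The gate decides whether up to 380 control children enter a second 30-day intervention and whether the trial goes on at all. A gate that has to be interpreted after the phase 1 data are known leaves that decision to judgement at the point where it should already be fixed.

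A smaller question concerns timing. The gate needs completed phase 1 data, whereas the per-child schedule shows no pause in which to wait for them.

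**Working it through.** **1. Outcomes against conditions.** No stated figure underlies the rule, so the check is one of logic. A two-sided test at 0.05 has three outcomes. Read literally, a result that is both not superior and statistically significant is a significantly worse one.

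| Phase 1 result for meditation | Stopping condition | Continuing condition | Stated action |
|---|---|---|---|
| Significantly better | not met | not met | none |
| Not significant | met | not met (significance is required) | terminate |
| Significantly worse | met | met | terminate and run phase 2 |

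The continuing condition is therefore a subset of the stopping condition: no result can start phase 2 without also ending the trial.

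**2. Could another reading rescue it?** One could take superior to mean better by more than some margin, so that a result could be significantly above zero yet not superior. The protocol states no margin. Even with one, a result beyond it would still have no stated action, and a significantly worse result would still meet both conditions.

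**3. Against the following paragraph.** That paragraph takes the experimental group's benefit as established. Under the continuing condition it cannot have been, so the paragraph and the condition cannot both describe the same route into phase 2. No other section restates or corrects the gate. The Discussion only describes phase 2 as a single-arm before-and-after study.

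**4. How often each outcome would arise (illustration).** The inputs come from the Sample size section: means 4.98 and 4.92, SDs 0.14 and 0.24, 760 and 380 subjects, 20% dropout. Assumptions: a single normal comparison with no centre effects.

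- Subjects remaining: 760 × 0.8 = 608 and 380 × 0.8 = 304.
- Standard error: √(0.14²/608 + 0.24²/304) = √(0.0000322 + 0.0001895) = 0.0149.
- Standardized difference: 0.06/0.0149 = 4.03.
- Chance of a significantly better result at +0.06: Φ(4.03 − 1.96) = Φ(2.07) = 98.1%.

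| True difference | Significantly better (no action) | Not significant (terminate) | Significantly worse (both actions) |
|---|---|---|---|
| +0.06 | 98.1% | 1.9% | about 0% |
| 0 | 2.5% | 95% | 2.5% |
| −0.06 | about 0% | 1.9% | 98.1% |

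**5. Timing.** Phase 1 takes about 1 month of training plus 3 months of follow-up, or 4 months per child. A child enrolled in December 2021 finishes it about April 2022. A child enrolled in September 2023 finishes about January 2024, which is 21 months later. The stated 8 months equals 2 × (1 + 3), so it fits one child's path through both phases with no gap. A gate based on complete phase 1 data would keep the earliest controls waiting about 21 months, and the schedule shows no such wait.

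**The case against.** The strongest reply is that this is a drafting slip. The following paragraph makes the intention fairly plain, and a sympathetic reader would treat the word 'not' in the continuing sentence as an accident. That is probably how it arose. Even so, it is current text (version 3.0), not an amendment history. It is also not a detail that an article leaves to a fuller document, because the rule is stated and conflicts with itself.

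It is also fair to say that the consequences are limited. Phase 2 follows the randomized comparison, and the slip leaves the phase 1 randomization, primary outcome and analysis untouched. That stands.

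Several stronger readings are tempting, and the documents do not support them:

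- A reader might infer that every phase 1 result has either two actions or none. A non-significant result has exactly one, termination, because the continuing sentence also requires significance.
- A reader might infer an unplanned interim look that inflates the type I error. The protocol describes no partial-data or school-by-school look and places the comparison after phase 1 is complete. Under the stopping sentence a non-significant look would end the trial, so it would not give a second chance at significance.
- A reader might infer that the calendar makes the gate unworkable. The 8 months can be read as one child's schedule, and Table 1 gives an order of visits without stating the interval before phase 2. What remains is a planning tension.
- A reader might take this to be the only decision threshold in the trial. The Statistical analysis section sets a significance level and response categories, and the Suspension criteria govern individual discontinuation.

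**Conclusion.** The gate is wrong as written. Of the three possible outcomes, one has two incompatible actions, one has a single clear action and one has none. At the planning difference, the outcome with no action is the one expected in about 98% of trials. That figure rests on the protocol's planning means and SDs, 20% dropout and no centre effects. The logical conflict needs none of these assumptions, only the two-sided 0.05 test and the plain meaning of the two sentences.

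The defect lies in the decision to stop or proceed and does not bias the phase 1 estimate or its error rate. It should still be corrected before phase 1 results are available, because it is an explicit rule that cannot be followed as written. The timing mismatch is secondary. It rests on reading the 8 months as a per-child schedule and on the recruitment dates in Trial status.

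**What to change.** Reconcile the stopping and continuing sentences with each other and with the paragraph that follows, so that a significantly better, a non-significant and a significantly worse result of the phase 1 primary comparison each lead to exactly one stated action. Which action belongs to which result is for the sponsor to state.

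In the same amendment, say that the comparison is made once, after the last phase 1 reading. Reconcile this with the 8-month schedule in the Intervention description and with the Table 1 sequence, so that any wait before phase 2 is visible.

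The cost is a few sentences and a timeline correction. No additional participants or measurements are needed, and the phase 1 analysis does not change.
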